## **Rationale & background information**

The basic goals of rehabilitation of patients with CLBP include the elimination of pain, restoring the lost range of motion of the spine, increasing the strength of the stabilising muscles of the trunk and overall improvement of functioning [1]. This can be achieved through various exercise protocols, manual therapy, various forms of massage, relaxation techniques, various soft tissue therapies and re-education of activities of daily living. Although there are numerous scientific studies on the effectiveness of various therapeutic methods in the treatment of LBP, the evidence of their effectiveness is highly obscure [2-7].

Deep tissue massage (DTM) is defined as the manual action of a therapist in the superficial and deep layers of muscles and fascia to relax, change abnormal patterns, eliminate tension and pain in the most ergonomic way [8]. DTM should be defined as a stand-alone therapy method using a specific set of techniques and principles. It is a safe form of massage with a wide range of applications, the techniques of which can be modified and improved to meet the needs of the patient. It is believed that DTM can reduce muscle tension, stretch muscles and fascia, improve joint range of motion, improve tissue blood supply, reduce pain and improve the overall function of the musculoskeletal system [9]. In the scientific literature, there is a small amount of research confirming the effectiveness of this therapeutic method.

In the scientific literature known to the authors, there are no studies evaluating the effectiveness of DTM in the context of changes in the parameters studied in the group of office workers with CLBP. The conducted experiment will therefore be innovative.

Hypothesis: The authors of the study hypothesized that DTM would increase all ranges of motion of the lumbar spine, increase the pressure pain threshold of longissimus muscle, and reduce back pain in a group of office workers with CLBP.

## **Study goals and objectives**

**The main objective:** The main objective of the study will be to assess the impact of deep tissue massage on subjective and objective parameters in a group of office workers with chronic low back pain.

### **Specific objectives:**

- Assessment of the impact of deep tissue massage on the mobility of the lumbar spine in all directions.
- Assessment of the effect of deep tissue massage on the discomfort threshold of tissue compression in the area of the longissimus muscle.
- Assessment of the impact of deep tissue massage on the level of pain.

## **Study design**

The conducted study will be a randomized clinical trial (triple-blind: participants, investigator, evaluator of results) with a parallel design. A simple randomization will be applied using a table of random numbers. All measurements will be carried out in the same place: the City Hall in Wolsztyn. A total of 40 people (aged 30-60) will participate in the study.

### **Inclusion Criteria:**

- CLBP group,
- office work for eight hours a day,
- moderate physical activity (eligibility criteria).

### **Exclusion criteria:**

- sciatica,
- neurological symptoms of the lower limbs (sensory and motor disorders),
- osteoporosis, lumbar spine surgery,
- Cancer,
- rheumatic diseases,
- cauda equina syndrome,
- pregnancy,
- during other CLBP therapy.

Participants will be randomized into two equal groups (experimental and control).

## **Methodology**

### **Intervention**

DTM will last 45 minutes. The entire therapy will include four treatments over a two-week period. The interval between treatments will be three days. The conducted therapy will include techniques for: quadratus lumborum muscle, erector spinae muscle, thoracolumbar fascia, iliopsoas muscle. All techniques will be performed on both sides of the patient's body. DTM will be performed by a physiotherapist with 5 years of experience.

## **Research methods:**

### **1) Electrogoniometer**

A Penny & Giles strain gauge electrogoniometer with two sensors (SG150 - two-axis, Q110 - single-axis) will be used. Measurements will be made in a standing position, in accordance with the measurement methodology according to Lewandowski [10]. All movements of the lumbar spine (forward flexion, backward flexion, right flexion, left flexion, right rotation, left rotation) will be tested. The average of the three measurements will be the result of mobility for a given direction. The sensors will be attached to the skin using Biometrics double-sided tape. The upper sensor (lower edge of the sensor) will be placed on the T12 spinous process, while the lower sensor (upper edge) will be placed on the base of the sacrum.

### **2) Algometer**

The Wagner Instruments algometer will be used to assess the subjective parameter, i.e. the first threshold of discomfort. The measurement site will be a point located on the longissimus muscle. Participants will be in the front lying position during the measurements. The sensor of the algometer will be applied from above and perpendicularly to the tested muscle (two fingers to the side of the L1 spinous process). Three measurements will be made alternately for both sides of the longissimus muscle under examination. From these measurements, mean values will be calculated, which will be the results for the right and left sides of the tested muscle.

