## **Data management and statistical analysis**

The adequate sample size was determined using the G\*Power 3.1.9 software. The standard threshold  $\alpha = .05$  was established; then the acceptable power level of the  $1-\beta = .90$  test and the expected moderate effect size  $\eta^2 = .30$  were determined for within-between interaction. The calculated total expected size of the sample is  $N = 32$ , i.e. 16 subjects in one research group, assuming that their number will not decrease during the study.

The collected data will be included in a database created with Excel 2019-2021, and calculations will be made using the Statistica 12.6 statistical software package (StatSoft. Inc.). Repeated measures ANOVA (PRE and POST) will be used to assess the effect of the DTM on the variables under study. In addition, a partial eta-square ( $\eta^2$ ) will be calculated - the so-called effect size measurement. For intra-group comparisons of the examined features (PRE and POST), the Student's t-test for dependent variables or the non-parametric Wilcoxon test for dependent pairs will be used. On the other hand, for intergroup comparisons, the Student's t-test for independent variables or the non-parametric U Mann-Whitney test for independent pairs will be used.

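### The pressure pain threshold is kept as two results per person, right and left, although treatment is bilateral and the hypothesis names no side; the two-side mean would give one test and somewhat better precision

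*Protocol*

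**What the plan says.** Protocol, section 2) Algometer: "Three measurements will be made alternately for both sides of the longissimus muscle under examination". The next sentence sets the outcome: "From these measurements, mean values will be calculated, which will be the results for the right and left sides of the tested muscle". So there are two threshold results per participant at each of the two visits.

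Protocol, Intervention: "All techniques will be performed on both sides of the patient's body".

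The hypothesis (Project summary, and Rationale & background information) is that the massage will "increase the pressure pain threshold of longissimus muscle, and reduce back pain in a group of office workers with CLBP". The matching specific objective is: "Assessment of the effect of deep tissue massage on the discomfort threshold of tissue compression in the area of the longissimus muscle". Neither names a side, and no inclusion or exclusion criterion depends on the side of the pain.

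Protocol, Data management and statistical analysis: "Repeated measures ANOVA (PRE and POST) will be used to assess the effect of the DTM on the variables under study". Time is the only repeated factor named. The section does not list the variables, and it gives no side factor, no combined threshold value and no rule for sides that disagree.

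**The concern.** The question about the threshold is posed once, for one muscle group in a person treated on both sides. The outcome is defined twice. If each side goes through the ANOVA as its own variable, three things follow.

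- Each test uses half of the readings already taken, so each is less precise than a test on their mean.
- Two tests at .05 serve one hypothesis, so the chance that at least one is falsely positive exceeds 5%.
- When one side reaches significance and the other does not, the plan does not say what the trial has found. A report could then describe an effect on one side only, although the true effect is the same on both.

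The same doubling would carry into the supplementary within-group and between-group comparisons in the same section.

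**Working it through.** **Inputs from the protocol.** Alpha .05, power .90, effect size given as .30 for the within-between interaction, calculated N = 32 (16 per group) and no dropout assumed (Data management and statistical analysis). 40 people (Study design), in two equal groups, hence 20 per arm.

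**Assumptions.** The protocol gives no right-left correlation of the change scores (r), so it is varied over .5, .7 and .9. Variances and true effects are taken as equal on the two sides.

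**Step 1: reproduce the plan's figure.** For two groups and two time points the interaction test has noncentrality λ = f² × N × 2 / (1 − ρ), where ρ is the PRE-POST correlation, with 1 and N − 2 degrees of freedom. With f = 0.30 and ρ = 0.5 (assumed), λ = 0.09 × 32 × 2 / 0.5 = 11.52. Power is 0.907, and 32 is the smallest even N that reaches .90. At N = 40, λ = 14.4 and power is 0.959. The figure is reproduced only when .30 is read as f. Read literally as eta-squared, it gives f = √(.3/.7) = 0.655 and N of 8 to 16 for ρ from .7 to 0. That is a separate matter and does not affect this point.

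**Step 2: put the planning effect on the change-score scale.** The interaction test is equivalent to a t-test on change, for which λ = d² × N / 4. Setting this equal to 0.36 × N gives d² = 1.44, so d = 1.2.

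**Step 3: precision of the two-side mean.** Var(mean) / Var(one side) = (1 + r) / 2. The effect size of the mean is 0.30 / √((1 + r) / 2).

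| r | Variance ratio | f for the mean | N for 90% power (one side: 32) | Power at N = 40 (one side: 0.959) |
|---|---|---|---|---|
| .5 | 0.75 | 0.346 | 24 | 0.990 |
| .7 | 0.85 | 0.325 | 28 | 0.980 |
| .9 | 0.95 | 0.308 | 30 | 0.967 |

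**Step 4: two tests for one hypothesis.** Simulation with 20 per arm, t-tests on change, two-sided .05, 40,000 trials per cell.

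| True d, both sides | r | One side significant, the other not | At least one side significant | Power, one side | Power, two-side mean |
|---|---|---|---|---|---|
| 0 | .5 | .082 | .091 | .050 | .051 |
| 0 | .7 | .068 | .083 | .050 | .049 |
| 0 | .9 | .042 | .071 | .050 | .049 |
| 0.8 | .5 | .294 | .840 | .692 | .813 |
| 0.8 | .7 | .224 | .807 | .697 | .762 |
| 0.8 | .9 | .130 | .756 | .692 | .714 |
| 1.2 | .5 | .064 | .992 | .961 | .990 |
| 1.2 | .7 | .055 | .985 | .957 | .980 |
| 1.2 | .9 | .031 | .973 | .957 | .965 |

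In the rows with d = 0 the power columns are the false-positive rate; the mean holds it at 5%. The columns can be checked against each other: at d = 1.2 and r = .5 both sides are significant in .927 of trials, and .992 − .927 = .065, which agrees with .064 up to rounding.

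**The case against.** The protocol never states outright that each side is tested alone. The algometer section describes how readings become side values, and the statistical section does not list its variables. Deriving one analysed value from two recorded sides is often left to a statistical analysis plan, and one may exist. This stands as a caution. It does not remove the point, because the protocol does more than stay silent: it names the right and left means as the results, and time as the only repeated factor.

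The size is also limited. At the effect that reproduces N = 32, one side already has about 96% power with 40 people, and the sides disagree in only 3% to 6% of trials. At r = .9 the mean saves 5% of the variance. The larger figures apply only if the true effect is smaller than planned. All of this stands.

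Reporting each side is a legitimate choice, and one-sided pain is not excluded, so equal effects are an assumption. This also stands, but it argues for showing the sides, not for testing a hypothesis without a side twice.

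A reader might extend the point to mobility, where "The average of the three measurements will be the result of mobility for a given direction". The documents do not support that. The hypothesis claims a gain in every range of lumbar motion, and the objective covers mobility in every direction, so separate results there match the stated aim. An argument that error in the neutral position cancels between right and left would need the measurement procedure. The protocol takes that from a cited source that is not at hand.

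**Conclusion.** The point holds for the pressure pain threshold. As written, the protocol most naturally leads to two tests of one hypothesis, with some loss of precision and no single answer. For r between .5 and .9:

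- the two-side mean has 0.75 to 0.95 of one side's variance;
- with no effect, at least one side is significant in about 9% to 7% of trials instead of 5%;
- with equal true effects and 20 per arm, the sides disagree in about 6% to 3% of trials at the planning effect (d = 1.2) and in about 29% to 13% at d = 0.8.

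These figures rest on an assumed r, equal variances and equal effects on the two sides. The planning effect also rests on reading .30 as f with a PRE-POST correlation of .5. A reader might infer that the two sides could show effects in opposite directions. The calculation does not show that: disagreement here means significant on one side and not significant on the other. This is a cheap improvement, not a flaw that undermines the trial.

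**What to change.** In section 2) Algometer, after the side means, define the analysed pressure threshold as the mean of right and left for each person and visit. In Data management and statistical analysis, state that the effect of the massage on the threshold is tested on that value, and that the single sides are reported descriptively. Leave the mobility directions in section 1) Electrogoniometer unchanged.

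The cost is one line of derivation and one sentence, with no new data and no added burden for participants. The downside is that a truly one-sided effect would appear only in the descriptive table; no such effect is hypothesised, and the treatment is given on both sides.

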### **3) Visual Analog Scale (VAS)**

This subjective tool is used to assess the level of pain. The subject will mark their pain level on a 10-cm scale, where zero is no pain and ten is the maximum pain they have ever felt. Current pain (VAS1), last week maximum pain (VAS2) and last week maximum pain sitting (>30 min) (VAS3) will be measured with this subjective tool.

In order to assess the impact of DTM therapy on the study population, two measurements will be made in time: 1) the day before the therapy; and 2) the day after treatment.

## **Safety considerations**

All planned measurement methods will be non-invasive and safe for health. DTM therapy is also safe and will be performed by an experienced physiotherapist. The authors will seek approval from the local bioethics committee. Experimental procedures will be carried out in accordance with the Declaration of Helsinki. Appropriate guidelines and regulations of the local institute will be strictly followed when conducting the study. The trial will be registered in the ClinicalTrials.gov clinical trials registry. Participants will be able to withdraw from participation at any stage during the study.

## **Follow-up**

Does not apply to this project. It is planned to perform two measurements in time: 1) the day before the therapy and 2) the day after the therapy. No follow up.

## **Data management and statistical analysis**

The adequate sample size was determined using the G\*Power 3.1.9 software. The standard threshold  $\alpha = .05$  was established; then the acceptable power level of the  $1-\beta = .90$  test and the expected moderate effect size  $\eta^2 = .30$  were determined for within-between interaction. The calculated total expected size of the sample is  $N = 32$ , i.e. 16 subjects in one research group, assuming that their number will not decrease during the study.

The collected data will be included in a database created with Excel 2019-2021, and calculations will be made using the Statistica 12.6 statistical software package (StatSoft. Inc.). Repeated measures ANOVA (PRE and POST) will be used to assess the effect of the DTM on the variables under study. In addition, a partial eta-square ( $\eta^2$ ) will be calculated - the so-called effect size measurement. For intra-group comparisons of the examined features (PRE and POST), the Student's t-test for dependent variables or the non-parametric Wilcoxon test for dependent pairs will be used. On the other hand, for intergroup comparisons, the Student's t-test for independent variables or the non-parametric U Mann-Whitney test for independent pairs will be used.

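### The stated planning effect, a moderate η² of .30, does not return the stated sample size of 32; the value is most likely a Cohen's f mislabelled as η²

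*Protocol*

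**What the plan says.** The whole justification is one short paragraph in the Protocol, under data management and statistical analysis. It opens "The adequate sample size was determined using the" G\*Power 3.1.9 program. It gives α = .05, power .90 "and the expected moderate effect size" η² = .30; these "were determined for within-between interaction. The calculated total expected size of the sample is" 32. That is split as "i.e. 16 subjects in one research group", "assuming that their number will not decrease during the study".

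The same section says of the analysis: "Repeated measures ANOVA (PRE and POST) will be used", with a partial η² reported as the effect size. The eligibility text adds "Participants will be randomized into two equal groups (experimental and control"), and the study design section plans 40 participants in total. The paragraph gives no pre-post correlation, does not say which of the software's effect-size conventions was used, and offers no SD or clinical basis for the effect.

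**The concern.** A reader who enters the printed inputs should get the printed N, and does not. Two things also sit badly together: an interaction explaining 30% of variance, and the adjective moderate. A figure of 0.30 called moderate reads more naturally as a Cohen's f.

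What is at stake is the meaning of the 90% power, because this paragraph is the only justification of the sample size. If the planning effect is mislabelled, nobody can tell from the Protocol what size of benefit the trial was built to detect. If the adjective is taken at face value, a non-significant result could be given more weight than it deserves.

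**Working it through.** **Inputs from the Protocol.** Two groups of equal size, two measurements (m = 2), α = .05, target power .90, η² = .30, no loss, stated N = 32, planned enrolment 40.

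**Assumed.** The pre-post correlation ρ, because none is given; 0.5 is the base case and a range is shown. The effect-size convention, because none is named; three were tried.

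**Test.** For a 2 × 2 group-by-time interaction, F has 1 and N − 2 degrees of freedom and noncentrality λ. N is raised in steps of 2 to keep the groups equal.

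- Convention A (default repeated measures): λ = f² · N · m / (1 − ρ). With m = 2 and ρ = 0.5, λ = 4 f² N.
- Convention B (partial η²): λ = f² (N − 2).
- Convention C (partial η²): λ = f² N.

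**Step 1. Reproduce 32.** Enter f = 0.30 under A with ρ = 0.5, so λ = 4 × 0.09 × N = 0.36 N.

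- N = 30: λ = 10.80, power 0.887.
- N = 32: λ = 11.52, power 0.907.
- N = 40: λ = 14.40, power 0.959.

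The smallest N reaching .90 is 32, exactly as stated.

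**Step 2. Use the effect as printed.** f² = .30 / .70 = 0.4286, so f = 0.655.

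| Convention | Power just below | Smallest N (power) | Power at N = 32 |
|---|---|---|---|
| A, ρ = 0.5 | 0.867 at 8 | 10 (0.950) | above 0.999 |
| B | 0.895 at 28 | 30 (0.917) | 0.934 |
| C | 0.893 at 26 | 28 (0.915) | 0.948 |

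None returns 32. Under A, even ρ = 0 needs only 16. Going the other way, f = 0.30 converts to η² = 0.09 / 1.09 = 0.083.

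**Step 3. How far the match depends on ρ.** With f = 0.30 under A, the required N is 62 at ρ = 0, 46 at 0.25, 38 at 0.4, 32 at 0.5, 26 at 0.6 and 20 at 0.7. Power at N = 32 is 0.64 at ρ = 0, 0.79 at 0.3, 0.91 at 0.5 and 0.99 at 0.7. The unstated correlation therefore drives the result.

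**Step 4. A scale that does not depend on the label.** Let d be the between-arm difference in mean change divided by the SD of the change score. Then λ = N d² / 4, whatever ρ is.

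- 90% power at N = 32 needs λ = 11.23, so d = 2 √(11.23 / 32) = 1.18.
- 90% power at N = 40 needs λ = 11.07, so d = 2 √(11.07 / 40) = 1.05.
- For d = 0.5, taken here as an assumed moderate effect: λ = 2.0 at N = 32, power 0.28; λ = 2.5 at N = 40, power 0.34.
- For d = 0.8: power 0.59 at N = 32 and 0.69 at N = 40.

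**Step 5. The planning effects on that scale.**

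- f = 0.30 under A at ρ = 0.5 is d = 2 √0.36 = 1.2. In raw-score SDs the difference in change is 4f = 1.2 as well. The two scales agree only at ρ = 0.5, where the change-score SD, √(2(1 − ρ)) raw SDs, equals 1.
- η² = .30 is d = 2 × 0.655 = 1.31 under C, and d = 4 × 0.655 = 2.62 under A at ρ = 0.5.

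On either reading the planned difference exceeds one SD of change.

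**The case against.** The strongest reply is that nothing about the design is shown to be wrong. The Protocol says it will report a partial η². Read that way, η² = .30 needs 28 or 30 participants; 32 has power 0.934 to 0.948, and the planned 40 has 0.976 to 0.981. On that scale f = 0.30 at correlation 0.5 is a partial η² of 0.36 / 1.36 = 0.265 under C, or 11.52 / (11.52 + 30) = 0.277 under B, so the suspected slip moves the planning value only from about .27 to .30. The f = 0.30 explanation also needs an assumed correlation and an assumed option.

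Most of this stands. The origin in f = 0.30 is a strong inference, not a documented fact. A reader might infer that the trial is underpowered for its stated effect; the Protocol does not support that, since 32 meets or exceeds the N required for η² = .30 under every convention tried. A reader might also infer that the mix-up is what confines 90% power to a very large effect. It is not: if f = 0.30 was entered, the planned effect is smaller than the printed η² = .30, and the 1.18 SD figure follows from N = 32 alone. Nor does the Protocol claim power for 0.5 SD, or say that a null result would exclude a moderate benefit.

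What the reply does not remove is that the printed inputs fail to give the printed N. Closeness to 30 does not settle it, because the usual calculation returns the smallest qualifying N, and under that convention this is 30. The adjective fits neither reading on the change-score scale.

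**Conclusion.** The point holds as an error in the stated planning effect, at should-fix level. With the printed η² = .30 the required N is 10, 28 or 30 depending on the convention; the stated 32 is reproduced exactly by f = 0.30 with correlation 0.5. The value is therefore most likely an f labelled as η². If it really was η² = .30, then N does not match it and moderate is the wrong word.

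A separate conclusion rests on N only: 90% power applies to a between-arm difference in change of about 1.18 change-score SDs at 32 and about 1.05 at 40. The 0.28 and 0.34 power figures depend on taking 0.5 change-score SD as moderate, which is an assumption made here. All figures assume two equal groups, two time points, α = .05 and no loss.

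**What to change.** Retrieve the software record and rewrite the sample-size sentence with the effect-size metric, the convention and the pre-post correlation actually used. If the record confirms f = 0.30 with correlation 0.5, state power 0.91 at 32 and 0.96 at the planned 40. These inputs were back-calculated here and should not be written in without that check.

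Delete the adjective moderate. Add that 40 participants give 90% power for a between-arm difference in change of about 1.05 change-score SDs, and name that SD explicitly so that it is not confused with the raw-score SD.

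The cost is a few sentences. Enrolment, test and analysis stay as they are. The price is a less favourable statement of the trial's sensitivity.

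### The repeated-measures ANOVA on PRE and POST is valid, but usually less precise than analysing POST adjusted for PRE, and the adjustment needs no new data

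*Protocol*

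**What the plan says.** The protocol's section on data management and statistical analysis names the model for the treatment effect: "Repeated measures ANOVA (PRE and POST) will be used to assess the effect of the DTM on the variables under study". The sample size rests on the same model: "the expected moderate effect size $\eta^2 = .30$ were determined for within-between interaction", with "The standard threshold $\alpha = .05$ was established" and "the acceptable power level of the $1-\beta = .90$ test". The result is given as "The calculated total expected size of the sample is $N = 32$ , i.e. 16 subjects in one research group", with no allowance for dropout ("assuming that their number will not decrease during the study").

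The section adds paired tests within each arm and independent-samples tests between arms. It does not say whether the between-arm tests are applied to POST or to change. No listed analysis uses PRE as a covariate.

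The design is randomised and parallel, with two measurement occasions (sections on study design and follow-up). Enrolment is larger than the calculated size: "A total of 40 people (aged 30-60) will participate in the study", and "Participants will be randomized into two equal groups (experimental and control"). Allocation is by simple randomisation from a random number table. There are 11 outcome variables: six directions of lumbar motion, two sides for pressure pain threshold and three VAS scores. Each is measured at PRE and POST.

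**The concern.** The planned model treats PRE as a second outcome. In a randomised two-arm trial with one baseline and one follow-up value, the interaction then compares mean change between arms, which fixes the coefficient of POST on PRE at 1. If the true regression slope is below 1, subtracting the whole baseline over-corrects. That adds noise, and any chance baseline difference between arms carries into the estimate. Analysis of covariance estimates the slope instead.

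Precision matters in a trial of 40 people. Every PRE value is already collected, so whatever is lost is lost without any saving.

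**Working it through.** **Inputs from the protocol.** α = 0.05, power 0.90, effect size 0.30 for the within-between interaction, calculated N = 32, planned N = 40 in two equal arms, two time points. **Not in the protocol, so assumed:** the PRE-POST correlation ρ, and equal variances at PRE and POST.

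**1. Reproducing N = 32.** For the interaction with two groups and m = 2 occasions, λ = N·m·f²/(1 − ρ) on 1 and N − 2 degrees of freedom. With f = 0.30 and ρ = 0.5, N = 32 gives λ = 32 × 2 × 0.09/0.5 = 11.52 and power 0.907. So N = 32 is reproduced if 0.30 is read as Cohen's f and ρ = 0.5. Read as η², 0.30 converts to f = √(0.30/0.70) = 0.655 and gives N = 10 at ρ = 0.5. The label is a separate matter. It is noted here because ρ = 0.5 and f = 0.30 are the inputs that reproduce the plan.

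**2. What f = 0.30 means.** In terms of a between-arm difference in change of δ (in SDs of the outcome), λ = N·δ²/[8(1 − ρ)]. Equating the two expressions gives δ = 4f = 1.2 SD.

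**3. Variance ratio.** With equal variances σ², the change-score variance is 2(1 − ρ)σ² and the ANCOVA residual variance is (1 − ρ²)σ². Their ratio is (1 + ρ)/2. Estimating the slope costs a factor 1 + 1/(N − 4), which is 1 + 1/36 = 1.028 at N = 40.

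| ρ | (1 + ρ)/2 | ratio at N = 40 | precision lost | reduction in SE |
|---|---|---|---|---|
| 0.3 | 0.65 | 0.668 | 33% | 18% |
| 0.5 | 0.75 | 0.771 | 23% | 12% |
| 0.7 | 0.85 | 0.874 | 13% | 6.5% |
| 0.8 | 0.90 | 0.925 | 7.5% | 4% |
| 0.9 | 0.95 | 0.976 | 2% | 1% |

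The reduction in SE is 1 minus the square root of the ratio at N = 40. A simulation of 40,000 trials per value gave ratios of 0.665, 0.766, 0.870 and 0.975 at ρ = 0.3, 0.5, 0.7 and 0.9, in agreement. The ratio reaches 1 where (1 + ρ)/2 × 37/36 = 1, that is at ρ = 0.946. Above that, adjustment gains nothing at this sample size.

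**4. Power at N = 40.** ANOVA interaction: λ = 40δ²/[8(1 − ρ)] on 38 df. ANCOVA: the same λ divided by the ratio at N = 40, on 37 df.

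| δ | ρ | λ, ANOVA | λ, ANCOVA | power, ANOVA | power, ANCOVA |
|---|---|---|---|---|---|
| 1.2 SD (f = 0.30) | 0.3 | 10.29 | 15.40 | 0.878 | 0.969 |
| 1.2 SD | 0.5 | 14.40 | 18.68 | 0.959 | 0.988 |
| 1.2 SD | 0.7 | 24.00 | 27.47 | 0.998 | 0.999 |
| 0.8 SD (assumed) | 0.3 | 4.57 | 6.84 | 0.55 | 0.72 |
| 0.8 SD | 0.5 | 6.40 | 8.30 | 0.69 | 0.80 |
| 0.8 SD | 0.7 | 10.67 | 12.21 | 0.89 | 0.93 |

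At f = 0.30 and ρ = 0.5, ANCOVA would reach 0.90 power with N = 26 instead of 32.

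**5. Baseline imbalance.** With 20 per arm, the standard error of the PRE difference is √(2/20) = 0.32 SD. A difference beyond 0.3 SD in either direction has about a 34% chance for any one outcome. Given such a difference, the change-score estimate is shifted by (1 − ρ) × 0.3 SD, or 0.15 SD at ρ = 0.5. ANCOVA removes this shift on average.

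**The case against.** The strongest reply is that the protocol states nothing wrongly. Under randomisation the interaction test has the correct type I error and is unbiased, and it matches the basis of the sample size. This stands. A reader might infer that the planned estimates are biased. That holds only conditionally on a realised baseline difference; over randomisation there is no bias.

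A reader might also infer that the trial is underpowered as planned. The protocol's inputs do not show this: with f = 0.30 and ρ = 0.5 the planned test already has 0.96 power at N = 40, above the 0.90 target. The 0.8 SD case is an assumption of this review, not a protocol figure.

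Two further limits stand. The protocol gives no ρ, so no single percentage can be stated as fact. Motion and pressure-threshold results are means of three readings, so correlations of 0.8 to 0.9 are plausible for 8 of the 11 variables, and there the gain is small. Nor is ANCOVA more precise at every ρ below 1. That claim needs equal variances and a large sample; if ρ × SD(POST)/SD(PRE) equals 1, change scores are as efficient asymptotically.

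It can also be said that covariates are often left to a statistical analysis plan, which is not shown. That carries less weight here, because the protocol itself names the effect model and sizes the trial on it.

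**Conclusion.** The point holds as an efficiency improvement. The named model is valid but usually gives away some precision and leaves chance baseline imbalance uncorrected. With equal variances and 20 per arm, the loss runs from about a third at ρ = 0.3 to almost nothing at ρ = 0.9, and is about 23% at the ρ that reproduces N = 32. The percentages refer to variance; the gain in standard error is roughly half as large.

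In power, the gain is about 3 percentage points on the inputs that reproduce the plan. It is about 11 points (0.69 to 0.80) if the true effect is 0.8 SD and ρ = 0.5. The documents support neither a finding of invalidity nor one of inadequate power.

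**What to change.** In the section on data management and statistical analysis, replace the sentence naming the effect analysis. For each outcome, fit a linear model of POST on group and PRE. Report the adjusted mean difference between arms with its 95% confidence interval, and the partial η² of the group term if an effect-size measure is still wanted. Keep the group-by-time interaction from the repeated-measures ANOVA as a sensitivity analysis.

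The cost is a change of wording. The PRE values are already planned for every participant and outcome, and no extra participants, visits or measurements are needed. N = 40 can stay as it is.
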